#### Participant timeline {13}

The timeline is presented in Table 2.

**Table 2 Tab2:**
[figure not shown]
Study timeline

t1 started to feed; t2 after 48 h of discontinuing non-invasive ventilation; t3 full oral feeding; t4 discharge; t5 follow-up at 6 months after discharge; t6 follow-up at 12 months after discharge; t7 at the corrected age of 18–22 months

#### Sample size {14}

The sample size was calculated using the online calculator available at http://powerandsamplesize.com/, based on the primary outcome measure of transition time—the duration time from the initiation of feeding to achieving full oral feeding. A two-sample independent means comparison method was applied for this calculation. The sample size calculation accounts are based on a type I error probability of 5% and a statistical power of 80%. According to our pilot study (*n* = 26), the mean transition times for the two groups were found to be μ1 = 11.36 days for the early OMIs group, μ2 = 13.40 days for the late OMIs group, with a *σ* = 4.99 days. The two groups were allocated in a 1:1 ratio; the initial calculation indicated a need for 126 participants per group. To account for potential dropouts or exclusions, the sample size was augmented by 10%, resulting in a total of 280 participants, or 140 participants per group.

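### The sample size section states 80% power, but its own inputs give 94 infants per group at 80%; the stated 126 per group is the 90% figure

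*Protocol article*

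**What the plan says.** All the figures are in the protocol article, Sample size {14}. The outcome is transition time in days, and "A two-sample independent means comparison method was applied for this calculation". The error rates are a "type I error probability of 5% and a statistical power of 80" per cent. The means come from a pilot of 26 infants: "μ1 = 11.36 days for the early OMIs group" and "μ2 = 13.40 days for the late OMIs group", with an SD of 4.99 days. On allocation the section says "The two groups were allocated in a 1:1 ratio". The result is that "the initial calculation indicated a need for 126 participants per group". For losses, "the sample size was augmented by 10%, resulting in a total of 280 participants, or 140 participants per group".

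The section does not say whether the 5% is one-sided or two-sided. The article gives no other value for power.

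**The concern.** The section prints every numerical input, names the method and states a result, so the calculation can be repeated in full, and the result does not follow from the inputs. This is not a detail left to a fuller document: no further text could make 80% power and 126 per group both true with these means and this SD.

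Two things are at stake. First, a reader of a null result would take the planned type II error to be 20%, when the evaluable sample gives about 10% at the assumed difference. Second, if 80% really was the target, the plan enrols 70 more preterm infants than that target needs. At the 12 per month given under Recruitment {15}, that is 280/12 = 23.3 months of recruitment instead of 210/12 = 17.5.

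**Working it through.** **Inputs (Sample size {14})**

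- Difference: 13.40 − 11.36 = 2.04 days
- SD: 4.99 days, so SD/difference = 4.99/2.04 = 2.446
- Type I error 5%, stated power 80%, allocation 1:1
- Loss allowance 10%
- Assumption: two-sided test, z = 1.960

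**Formula for two independent means, per group**

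n = 2 × [(z for alpha + z for power) × SD / difference]²

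**The plan's figure, 126.** It is reproduced at 90% power (z = 1.282):

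n = 2 × (3.2415 × 2.446)² = 125.7, rounded up to **126**. Then 126/(1 − 0.10) = 140 per group and 280 in total, which are the printed figures.

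**The stated power, 80%** (z = 0.842):

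n = 2 × (2.8016 × 2.446)² = 93.9, rounded up to **94**. Then 94/0.9 = 104.4, so 105 per group and 210 in total.

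The gap is 126 − 94 = 32 per group before losses and 280 − 210 = 70 in total (280/210 = 1.33).

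**Power actually obtained.** The standard error with 126 per group is 4.99 × √(2/126) = 0.629 days. Then 2.04/0.629 − 1.960 = 1.285, which gives 90.1% power.

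| Evaluable per group | Normal approximation | t distribution |
|---|---|---|
| 126 | 90.1% | 89.8% |
| 140 (no losses) | 92.8% | 92.6% |

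**Other readings tried, to see whether 126 can arise at 80% power**

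| Reading | n per group |
|---|---|
| Two-sided 5%, t distribution | 95 |
| One-sided 5% | 74 |
| Two-sided alpha 0.025 | 114 |
| Two-sided alpha 0.01 | 140 |
| 94 divided by a rank-test efficiency of 0.955 or 0.864 | about 98 or 109 |

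None gives 126. A one-sided test widens the gap, and at 90% power it gives 103. With 80% power and 126 per group, the difference would have to be 2.8016 × 0.629 = 1.76 days, or the SD 2.04 × √63 / 2.8016 = 5.78 days. The section gives neither value.

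**The case against.** The strongest reply accepts the arithmetic and disputes its importance.

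- **The error is in the safe direction.** On the stated inputs the trial has more power than claimed. The loss allowance is applied consistently, 280 matches the allocation list in Sequence generation {16a}, and 12 per month over 24 months would yield 288. No test or decision rule uses the stated power. All of this stands, and it is why enrolment need not change.
- **The inputs are themselves uncertain.** With a pilot of 26 infants, and assuming normal data and a pooled SD on 24 degrees of freedom, an approximate 95% interval for the SD runs from 3.9 to 6.9 days. An SD of 5.78, at which 126 gives 80% power, lies inside it. A null result would also be read mainly from its confidence interval. This limits how literally either power figure should be taken. It does not rescue the calculation, which uses 4.99.
- **The article does not show which figure is wrong.** The power may have been misreported, but a mean or the SD could instead have been mistranscribed. This stands. The exact match of 126, 140 and 280 makes 90% the likely figure, but that is an inference, so the sponsor must confirm it.
- **The registry and ethics submissions are not at hand.** Whether they repeat 80% is unknown, and nothing here rests on them.

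**Conclusion.** The statement is wrong as written: 80% power and 126 per group cannot both hold with a difference of 2.04 days and an SD of 4.99 days. The correct pairs are 80% with 94 per group, or 90% with 126 per group. The conclusion assumes a two-sided 5% test of two independent means with equal allocation; a one-sided test makes the mismatch larger. The normal approximation and the t distribution differ by only about one infant per group.

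It is an error in a core design figure, but not one that threatens the trial's ability to detect the assumed difference. Restating the power as about 90% is true of the printed inputs and the planned size, whichever figure the authors had in mind.

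**What to change.** Check the inputs that were entered in the online calculator. If they are the printed means and SD, keep 280 infants and replace the power statement with wording such as:

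> Two-sided type I error 5%, power 90% (normal approximation), difference 2.04 days, SD 4.99 days: 126 evaluable infants per group, 140 per group and 280 in total after allowing for 10% loss.

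By the t distribution, 126 per group gives 89.8% and a full 90% needs 127, so either name the approximation or write about 90%. If the check shows that a mean or the SD was mistranscribed, correct that input instead and recompute.

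Use the same figure in the final report, and check that the registry entry agrees. The article's section on communicating amendments {25} already provides for a registry update. The cost is one sentence, with no change to enrolment, allocation or analysis.

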#### Recruitment {15}

Recruitment is currently in progress. We estimate an average enrollment of 12 participants per month based on the anticipated number of preterm admitted to the NICU and recruitment rates observed in our previous pilot studies. The research team will maintain daily checks of the electronic medical record system and communicate with the clinical team to identify infants who potentially meet the eligibility criteria, along with their parents. The research nurse will approach the eligible infants' parents, provide them with information, and obtain their consent.

## Assignment of interventions: allocation

### Sequence generation {16a}

We employ the method of generating random numbers using the web page ( https://www.random.org/) through a sequence generator for the purpose of random allocation. The 280 eligible study subjects who meet the inclusion criteria will be sequentially assigned numbers ranging from 1 to 280, corresponding to their order of admission. Each number assigned to a participant corresponds to a unique random number generated by the website. Based on the outcome of this random number generation, participants assigned odd numbers will be placed in the early OMIs group, whereas those with even numbers will be categorized into the late OMIs group.

### Concealment mechanism {16b}

The randomization scheme will be concealed by placing the random allocation sequences in opaque envelopes. Each envelope corresponded to a sequential number (aligned with the admission order). The management of the randomization scheme was independently handled by a research nurse not involved in the intervention. After obtaining informed consent from the participants, they will be allowed to open the envelopes to reveal their assigned group upon which the grouping result was obtained.

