## Trial design {8}

This study employs a single-blind, randomized, and controlled trial design, assigning preterm infants to one of two groups: early OMIs or late OMIs. The flow chart is presented in Fig. 1.

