### Implementation {16c}

After obtaining consent and before proceeding with the medically necessary procedure, the research nurse will perform randomization of the preterm to determine the allocation of the study intervention.

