## Assignment of interventions: blinding

### Who will be blinded {17a}

Blinding will be implemented for study participants, their families, data collectors, and statisticians, meaning that neither the subjects nor their families, data collectors, and statisticians are aware of the group assignments in the trial.

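### As worded, the concealment section lets parents open the allocation envelope, which contradicts the stated blinding of families

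*Protocol article*

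**What the plan says.** Three adjoining sections of the Protocol article describe how allocation is revealed and who may know it.

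- **Concealment mechanism {16b}.** Allocations are held in opaque, numbered envelopes. On who looks after them: "The management of the randomization scheme was independently handled by a research nurse not involved in the intervention". On who opens them, once the participants have consented: "they will be allowed to open the envelopes to reveal their assigned group upon which the grouping result was obtained".
- **Implementation {16c}.** After consent, "the research nurse will perform randomization of the preterm to determine the allocation of the study intervention".
- **Who will be blinded {17a}.** "Blinding will be implemented for study participants, their families, data collectors, and statisticians". The section then spells out what this means: "neither the subjects nor their families, data collectors, and statisticians are aware of the group assignments in the trial".

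Two other sections bear on the reading. Recruitment {15} has the research nurse approach the infants' parents, "provide them with information, and obtain their consent". Trial design {8} gives the label: "This study employs a single-blind, randomized, and controlled trial design".

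**The concern.** A family that opens the envelope is not blinded. The article names families among the groups kept unaware, so a reader of the trial report would credit the trial with a safeguard that its own procedure removes.

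Parents can act on knowing the arm in three ways:

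- **Withdrawal.** They may take the infant out of the study whenever they wish (Criteria for discontinuing or modifying allocated interventions {11b}). Parents who know that the infant is in the late group may do so more often.
- **Follow-up.** Feeding and growth are assessed at 6 and 12 months corrected age, and neurodevelopment at 18 to 22 months (Outcomes {12}). Attendance after discharge depends on the family.
- **Disclosure.** A parent who knows the group can mention it to a data collector who is meant not to know it.

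Any of these could differ between arms. The analysis could not repair that afterwards, and a family that has seen the allocation cannot be blinded again.

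**Working it through.** No arithmetic applies: the point depends on no error rate, effect size or sample size. The check is to set the sections side by side.

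1. **Who are the people in {16b} who open the envelope?** The sentence is "After obtaining informed consent from the participants, they will be allowed to open the envelopes to reveal their assigned group". The noun before the pronoun is the participants. The group revealed is the openers' own, which suits participants, since staff are not assigned to a group. The sentence gives permission, which suits a family better than a nurse whose task is to randomise.

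2. **Who are the participants in practice?** Eligibility criteria {10} require enrolment within the first 72 h of life, so the subjects are newborns. Recruitment {15} has the parents give consent. Participants who consent and then open an envelope can only be the parents.

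3. **Does {17a} allow this?** No. It lists families as blinded and defines that as being unaware of group assignment.

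4. **Does {16c} resolve the conflict?** Only in part. It names the research nurse as the person who randomises. It does not say that she opens the envelope, or that the result is withheld from the family.

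5. **Does any other section resolve it?** No. Who will take informed consent {26a} and Recruitment {15} deal with consent only. Procedure for unblinding if needed {17b} expects no need to reveal allocation before analysis and says nothing about the envelope.

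| Reading of {16b} | Consistent with {17a}? | Consistent with {16c}? | Text needs correction? |
|---|---|---|---|
| Parents open the envelope (plain wording) | No | Poorly | Yes |
| Research nurse opens it (possible intent) | Yes, if she does not tell the family | Yes | Yes: {16b} does not say so, and no section says the result is withheld |

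On either reading {16b} has to be reworded.

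**Which outcomes are exposed?** The primary outcome is the number of days from the start of feeding to full oral feeding. Full oral feeding is defined as 120 ml/kg/day with no tube feeding for at least 48 h. It is a ward measurement based on volume, and parents do not report it. Oral intake and feeding time for the feeding-performance outcomes are recorded by nursing staff from outside the study. What parents know has its most direct route to withdrawal, to attendance after discharge, and to data collectors who learn the arm from them.

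**The case against.** The strongest reply is that no sentence says outright that parents open envelopes. The wording is loose. The sentence before it names the nurse who manages the scheme, {16c} has the research nurse randomise, and {17a} says that families are unaware. Two explicit sections therefore point to staff, and one pronoun points the other way. That intent is quite possible, so the finding has to be put as a conflict on the plain wording and not as proof that families have been unblinded. It does not rescue the text, because staff who follow {16b} literally would show each family its group.

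It is also fair to say that both arms receive the same programme and differ only in start time, so the motive to withdraw is weaker than in a comparison of treatment with no treatment. That lowers the likely size of the effect but does not remove the contradiction.

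A reader might infer more than the article supports:

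- **That the case for having no interim analysis falls.** Interim analyses {21b} is concerned with disclosing trial data by allocation before the analysis. One family's knowledge of its own infant's group is a different matter, and the section gives two further reasons.
- **That allocation concealment failed.** In {16b} the envelope is opened after consent. The wording does not show that anyone could foresee the next allocation.
- **That data collectors and statisticians are unblinded too.** Their blinding is stated separately and does not depend on who opens the envelope. Disclosure by parents is a risk, not a described event.
- **That every family has been unblinded.** The article does not report what has been done with infants already enrolled.

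**Conclusion.** The point holds as an internal contradiction: {16b} on its plain wording, {16c} and {17a} cannot all be carried out. If {16b} is followed, the family blinding that the article claims does not exist. If it is not followed, {16b} misdescribes the procedure.

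The size of any bias cannot be derived from the document. In direction, the risk lies in differential withdrawal, follow-up attendance and disclosure of the arm to data collectors, and much less in the primary outcome.

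The conclusion rests on two assumptions: that the participants who consent are the parents, which Recruitment {15} supports, and that the pronoun refers to them, which is the natural grammar but perhaps not the intent. The need to correct the text depends on neither, because the article nowhere says both who opens the envelope and that families are not told the result.

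**What to change.** Reword Concealment mechanism {16b} so that, after consent, the research nurse who manages the scheme and takes no part in delivering OMIs opens the next envelope. She gives the result only to the nurses who deliver OMIs, and not to parents or data collectors. Align Implementation {16c} with this.

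If families cannot in practice be kept unaware, take them off the list in Who will be blinded {17a} and do not claim family blinding in the report. Either route removes the contradiction.

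For infants already enrolled, record whether the parents saw the allocation, and report the number by arm.

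The cost is an amendment to the wording, an instruction to staff and one extra item of data per enrolled infant. The article describes the nurse who manages the scheme as separate from the intervention only. It does not say that she is separate from consent or from outcome collection, and other sections give consent and the fidelity checklist to a research nurse without saying whether it is the same person. If the sponsor wants that further separation, it has to be arranged and cannot be assumed to be in place. Recruitment was under way when the article was written, so the change should be made promptly.

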### Implementation {16c}

After obtaining consent and before proceeding with the medically necessary procedure, the research nurse will perform randomization of the preterm to determine the allocation of the study intervention.

## Assignment of interventions: blinding

### Who will be blinded {17a}

Blinding will be implemented for study participants, their families, data collectors, and statisticians, meaning that neither the subjects nor their families, data collectors, and statisticians are aware of the group assignments in the trial.

### Procedure for unblinding if needed {17b}

We do not expect the need to reveal the data’s allocation status before conducting the analyses.

## Data collection and management

### Plans for assessment and collection of outcomes {18a}

The measurement of baseline data takes approximately 15 min, NOMAS assessment requires 2 to 4 min, measuring height and head circumference takes 3 to 5 min, and the total data collection time is approximately 30 min. Premature infants will be followed up until completing neurodevelopmental assessment at 18–22 months of age.

### Plans to promote participant retention and complete follow-up {18b}

Free consultation and follow-up will be provided to patients and their families during the study.

### Data management {19}

Establishment of the data monitoring committee to strictly control the data collection. Demographic and background clinical data describing the sample that will be collected from the electronic medical record system will include maternal parity, maternal age, maternal disease, pregnancy complications and co-morbidities, conception method, delivery method, infant GA at birth, infant birth weight, infant height, infant head circumference, infant Apgar scores, infant sex, diagnoses, and so on.

### Confidentiality {27}

The identities of study participants will remain confidential and will not be disclosed in any research reports or publications. All study participant data and videotapes will be securely stored within a locked metal cabinet at the NICU. To further protect privacy, participant names will be completely removed and replaced with a unique code for identification purposes. This code will be securely stored within a locked metal cabinet in the same place. All research records will be retained for a minimum period of 10 years and will only be accessible to authorized research staff.

### Plans for collection, laboratory evaluation, and storage of biological specimens for genetic or molecular analysis in this trial/future use {33}

N/A: There will be no collection of biological specimens as part of this trial.

## Statistical methods

### Statistical methods for primary and secondary outcomes {20a}

The intention-to-treat analysis (ITT) will be the main analysis, with a per-protocol set (PPs) analysis conducted simultaneously. A significance level of *P* < 0.05 will be considered statistically significant. In the ITT analysis, all subjects will be included in the group to which they are assigned, regardless of whether they completely received the intervention. (1) Descriptive statistics will be used to summarize baseline characteristics. Continuous variables will be presented as Mean ± Standard deviation and categorical variables as percentages (%). (2) For comparisons between groups, Student *t*-tests will be applied for continuous variables, and chi-square tests will be utilized for categorical variables. (3) Assessment of efficacy: for continuous variables, independent Student *t*-tests will be employed for evaluation if conditions are met. (4) For data that do not follow a normal distribution, ordinal data, or data with significantly unequal variances, non-parametric tests will be used. The statistical analysis will be conducted using the medical statistical software SPSS 23.0 (SPSS, IBM Corporation, Armonk, NY, USA).

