### Eligibility criteria {10}

Inclusion criteriaDiagnosis as preterm, with a birth weight of less than 2500 g, and gestational age ranging from 29^+0^ to 34^+6^ weeks.Stability of vital signs.Absence of major congenital anomalies, such as congenital heart disease, or congenital digestive tract malformations.Requirement non-invasive ventilation support, including the use of a high-flow nasal cannula.Enrollment within the first 72 h of life.

Exclusion criteriaRequirement of mechanical ventilation.Severe asphyxia.Prior enrollment in other studies.Diagnosis of necrotizing enterocolitis (NEC).Diagnosis of periventricular leukomalacia (PVL).Diagnosis of intracranial hemorrhage grade III or higher.Need for reinitiation of non-invasive ventilation support after the start of the OMIs.

There are termination criteria and they are as follows: (1) Occurrence of severe adverse events and complications during the trial. (2) Withdrawal of consent by the parents of the subject. Patients who enter the trial but fail to complete it due to any reason will be considered dropout cases. This includes cases where the doctor determines that the subject has withdrawn from the trial, as well as cases where the subject withdraws on their own, regardless of the timing or reason for withdrawal. All data on the infants will still be recorded.

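### Multiple births may be enrolled and are randomised infant by infant, but the planned t-test ignores the sibling correlation and gives up some precision on the primary outcome

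*Protocol article*

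**What the plan says.** All references are to the protocol article.

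- **Eligibility criteria {10}.** Infants enter on prematurity, "with a birth weight of less than 2500 g, and gestational age ranging from" 29+0 to 34+6 weeks, together with stability, respiratory and timing conditions. None of the criteria concerns plurality or limits entry to one infant per mother.
- **Sequence generation {16a}.** The 280 infants "will be sequentially assigned numbers ranging from 1 to 280, corresponding to their order of admission". Each number has its own random number, whose parity decides the arm. There is no rule for siblings.
- **Sample size {14}.** "A two-sample independent means comparison method was applied for this calculation".
- **Statistical methods for primary and secondary outcomes {20a}.** "Assessment of efficacy: for continuous variables, independent Student" t-tests are used if their conditions are met, with non-parametric tests otherwise and chi-square tests for categorical variables.
- **Methods for additional analyses {20b}.** Linear or logistic regression may be added if required. No cluster term is named.

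**The concern.** Siblings share a mother and the same gestational age, and gestational age is the basis of the protocol's only named subgroup analysis. Their transition times are therefore likely to be positively correlated.

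Under infant-level allocation, about half of twin pairs are split between arms and about half share an arm. A split pair is in effect a matched comparison, yet the t-test handles it as two unrelated infants. A pair in the same arm holds less information than two unrelated infants, yet it is counted in full. A method that weights the two kinds of pair correctly estimates the treatment difference more precisely from the same infants. What is at stake is that precision, on the primary outcome and on the other continuous outcomes.

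**Working it through.** **1. The plan's own figure.** The inputs from Sample size {14} are "11.36 days for the early OMIs group", "13.40 days for the late OMIs group" (difference 2.04 days), SD 4.99 days and 1:1 allocation, with the calculation "based on a type I error probability of 5% and a statistical power of 80"%. The formula per group is n = 2(z₁₋α/₂ + z₁₋β)² × SD² / difference².

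- Two-sided 5%, 80% power: 2 × (1.960 + 0.842)² × 4.99² / 2.04² = 93.9, so 94.
- Two-sided 5%, 90% power: 2 × (1.960 + 1.282)² × 4.99² / 2.04² = 125.7, so 126.

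The stated 126 per group therefore matches 90% power, not the stated 80%. The dropout step reproduces: 126 / 0.90 = 140 per group. For this point, the baseline is about 90% power at 126 per group if infants are independent.

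**2. Error rate of the t-test under the documented allocation.** With each infant allocated separately, same-arm pairs add a positive covariance to the variance of the difference and split pairs add a negative one. The two cancel on average. Simulation with 280 infants (20,000 runs per scenario; 10–40% of infants in pairs; correlation 0.3–0.8; balanced and coin-flip allocation) gave rejection rates of 4.6–5.3% under the null. The nominal 5% holds.

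**3. Information left unused.** Let f be the share of infants in complete enrolled pairs and r the sibling correlation. The documents give neither, so f = 0.10–0.25 and r = 0.3–0.7 are assumptions. Relative to the independent analysis, the information per infant is 1/(1 − r) in a split pair and 1/(1 + r) in a same-arm pair. Their mean is 1/(1 − r²), so

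relative information = (1 − f) + f/(1 − r²).

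| f | r = 0.3 | r = 0.5 | r = 0.7 |
|---|---|---|---|
| 0.10 | 0.90 + 0.10/0.91 = 1.010 | 0.90 + 0.10/0.75 = 1.033 | 0.90 + 0.10/0.51 = 1.096 |
| 0.25 | 0.75 + 0.25/0.91 = 1.025 | 0.75 + 0.25/0.75 = 1.083 | 0.75 + 0.25/0.51 = 1.240 |

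The gain is about 1–24%, and about 3–8% at r = 0.5.

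**4. What this means for power.** Multiplying 126 per group by the relative information and recalculating power for 2.04 days:

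- r = 0.5: from 90.1% to 91.0% (f = 0.10) or 92.2% (f = 0.25).
- r = 0.7: from 90.1% to 92.5% (f = 0.10) or 95.1% (f = 0.25).

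These figures treat r as known. Simulation with 252 infants and r estimated from the data gave similar gains, about 1–2 points at r = 0.5 and 2–5 points at r = 0.7. The mixed model held about 5% error and lost nothing when r was zero.

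**5. The bounding case that the protocol does not contain.** If every pair were placed in one arm, the design effect would be 1 + f × r. At f = 0.25 this is 1.125 (r = 0.5) or 1.175 (r = 0.7), and the actual two-sided error 2Φ(−1.96/√DE) is 6.5% or 7.1%. With 65% of pairs together, f = 0.25 and r = 0.5, the design effect is 1 + 0.125 × 0.30 = 1.0375 and the error about 5.4%.

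**The case against.** The strongest reply is that the planned test is valid and the trial has room to spare. The t-test keeps its level, and 126 per group already gives about 90% power for the stated difference. A more precise method is then a refinement, and no conclusion on the primary outcome is endangered. This stands, and it limits the weight of the point.

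The size of the gain is also uncertain. Only pairs with both siblings enrolled count, and each sibling must separately meet the respiratory, asphyxia and 72-hour conditions. The relevant share is therefore at or below the share of twins among eligible infants. Adjustment for gestational age would lower the remaining correlation. This stands too, and is why the range reaches down to 1%.

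Two further limits are fair. The proposed model does not reach the non-parametric branch of {20a}. And the absence of a plurality field cannot be inferred from Data management {19}, because its list of variables is left open-ended.

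An unseen analysis plan might handle siblings. However, {20a} names the independent test outright, so the point rests on what the protocol states and not on an omission.

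A reader might infer something stronger: that correlated siblings push the type I error above 5%, or that the sample needs a design effect. The documents do not support either. Siblings who share an arm by chance do no harm to the level (step 2). Inflation needs systematic placement of siblings together, and no section provides for that: {16a} allocates each infant by its own number, and Concealment mechanism {16b} ties opaque envelopes to that number.

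**Conclusion.** The point holds as a loss of precision only. The stated population can contain sibling sets, and the stated test makes no use of them. With 10–25% of infants in complete pairs and a sibling correlation of 0.3–0.7, the unused information is about 1–24%, and about 3–8% at correlation 0.5. Both inputs are assumptions. The calculation also takes pairs only and normally distributed outcomes.

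The 5% error rate is not in question under the documented allocation. The 6.5–7% in step 5 is an upper bound for all pairs placed together at a 25% share, not a description of this trial. The change is worth making because it costs almost nothing, not because the planned analysis is invalid.

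**What to change.** - In Data management {19}, name a mother identifier among the variables collected.
- In Statistical methods {20a}, replace the independent t-test for transition time and the other continuous outcomes with a linear mixed model: arm as fixed effect, random intercept for mother, singletons as clusters of one. The MIXED procedure in the named software fits it. State what applies if the non-parametric branch is used.
- For binary outcomes, use GEE clustered by mother in place of the chi-square test.
- Leave the individual randomisation in {16a} as it is. It protects the error rate and produces the split pairs from which the gain comes.

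The amendment should be made before data are analysed by group; Trial status says that recruitment is still in progress. The cost is one field from the medical record and a change of wording, with no extra infants, staff or procedures. The downside is a slightly more complex model, with little or no gain if few sibling pairs are enrolled or the correlation is low.
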